## 3 Objectives

The primary objective of this trial is to demonstrate superiority of a treatment regimen with Certican with respect to the renal function at 6 months after renal transplantation (Tx) assessed by glomerular filtration rate (GFR) – Cockcroft-Gault method - as compared to the standard regimen in *de novo* senior renal transplant recipients.

Secondary objectives of this trial are:

- to assess renal function by GFR – MDRD and Nankivell method – at Month 6 post Tx
- to assess renal function by serum creatinine at Month 6 post Tx
- to assess efficacy (biopsy proven acute rejection, graft loss, death) at Month 6
- to assess occurrence of treatment failures up to or at Month 6, while treatment failure is defined as a composite endpoint of biopsy proven acute rejection, graft loss, death, loss to follow up and discontinuations due to lack of efficacy or toxicity, or conversion to another regimen (at least one condition must be present)
- to assess evolution of renal function (creatinine slope) between Week 7 (randomization) and Month 6
- to assess CD25 saturation on lymphocytes
- to assess safety and tolerability at Month 6:
  - AE/SAE
  - incidence of infections (CMV, BK virus)
  - tumor incidence
  - cardiovascular risk
  - occurrence of proteinuria
  - NODM

## 4 Study design

This is a prospective, multi-center, randomized, controlled, open label study in *de novo* senior renal transplant recipients. Approximately 240-260 patients fulfilling the inclusion and exclusion criteria will be randomized in a 1:2 fashion to either Control or Certican arm.

Once consent is obtained, baseline data will be collected to determine each patient's eligibility for study participation. Baseline (BL) assessment will be performed prior to transplantation.

For the first six weeks post transplantation, all study patients will receive induction therapy with Simulect® (2 x 20 mg (day 0 [2 hrs prior to Tx] and day 4 post Tx) and will commence on an immunosuppressive regimen consisting of Myfortic® "loading dose" + Sandimmun® Optoral (based on C0-h level) with corticosteroids (steroid withdrawal after week 2).

At BL2 (Week 7, Visit 3), patients whose eligibility is confirmed by additional in- and exclusion criteria will be randomized and hence allocated to one of the two treatment groups in a 2:1 ratio.

**Group 1: Certican® switch immunosuppressive therapy in the following steps**

- Step 1: Day 1 morning: Myfortic® + Sandimmun® Optoral  
Day 1 evening: Myfortic® + Sandimmun® Optoral + Certican® (3 mg)
- Step 2: Day 2 morning: Myfortic® + Certican® (1.5 mg)  
Day 2 evening: Myfortic® + Certican® (1.5 mg)
- Step 3: Day 3 morning: Myfortic® + Certican® (TL 5 – 10 ng/mL)

**Group 2: Control maintain prior immunosuppressive regimen consisting of Myfortic® + Sandimmun® Optoral**

In group 1, step 1 of the therapy switch will be performed the day after randomization and will be continued on Day 2 with step 2. The therapy switch will be completed on Day 3 with step 3.

Patients randomized to Certican group will receive two additional doses of Simulect® (each 20 mg) as rejection prophylaxis on Week 7 and 12.

The established treatment will be continued until month 6 (final assessment of the core trial). Control assessments will be performed at Week 12, 18 and 24 (end of study and early discontinuation) post Tx. Renal function (creatinine, GFR) as well as safety and efficacy measures will be assessed at every study visit.

In the event of suspected acute rejections, renal biopsies will be performed.

Additionally, on day 7 ± 2 after randomization a blood level control will be performed.

Statistical analysis and report writing will be performed when all patients have completed Month 6 after Tx assessment (or discontinued the study prematurely).

An independent Safety-Monitoring-Board will review the safety data every 3 months during the recruitment phase and every 6 months thereafter, until all patients have completed the study treatment (Month 6).

**Table 4-1 Study outline**

| Phase   | Prephase |   | Study Drug Treatment |             |    |    |    |
|---------|----------|---|----------------------|-------------|----|----|----|
| Period  | BL1      |   | BL2                  | Maintenance |    |    |    |
| Visit   | 1        | 2 | 3                    | 4           | 5  | 6  | 7  |
| Week    | 0        | 2 | 7                    | 8           | 12 | 18 | 24 |
| Month   |          |   |                      |             |    |    | 6  |
| Random. |          |   | X                    |             |    |    |    |

| Treatments                 |                                                 |                        |                                 |                                  |                 |
|----------------------------|-------------------------------------------------|------------------------|---------------------------------|----------------------------------|-----------------|
| Certican group             |                                                 |                        |                                 |                                  |                 |
| - Simulect®                | 20 mg day 0
(2hrs prior Tx)
day 4 post Tx | none                   | 20 mg
(week 7)               | none                             | 20 mg (week 12) |
| - Myfortic® 2)             | 2880 mg/day                                     | 2160 mg/day            | 1440 mg/day                     |                                  |                 |
| - Sandimmun®
Optoral 1) | acc. to blood
level                          | acc. to blood
level | none                            |                                  |                 |
| - Corticosteroids          | 5 mg/day
(minimum
dose)                   | removal                | none                            |                                  |                 |
| - Certican®                | None                                            | none                   | introduction                    | acc. to blood level (5-10 ng/ml) |                 |
| Control group              |                                                 |                        |                                 |                                  |                 |
| - Simulect®                | 20 mg day 0
(2hrs prior Tx)
day 4 post Tx | none                   | none                            |                                  |                 |
| - Myfortic® 2)             | 2880 mg/day                                     | 2160 mg/day            | 1440 mg/day                     |                                  |                 |
| - Sandimmun®
Optoral 1) | acc. to blood
level *                        | removal                | Acc. to blood level (see below) |                                  |                 |
| - Corticosteroids          | 5 mg/day
(minimum
dose)                   | removal                | none                            |                                  |                 |
| - Certican®                | None                                            | none                   | none                            |                                  |                 |

BL1 = Baseline visit 1: is to be performed prior to transplantation

---

|                                 |                                                                                                                                                                                                                                                |
|---------------------------------|------------------------------------------------------------------------------------------------------------------------------------------------------------------------------------------------------------------------------------------------|
| BL2                             | = Baseline visit 2: day of randomization                                                                                                                                                                                                       |
| Dosages:                        | The given total daily dosages of the immunosuppressive drugs (Myfortic ® , Sandimmun ® Optoral, Certican ® ) should be divided into 2 (equal) doses, applied 12 hours apart (i.e., 08:00 a.m. and 08:00 p.m.) |
| 1) Optoral ® Dosage: |                                                                                                                                                                                                                                                |
|                                 | Week 1 – Week 4: C0-h 150 – 200 ng/ml                                                                                                                                                                                                          |
|                                 | Week 5 – Week 18: C0-h 100 – 150 ng/ml                                                                                                                                                                                                         |
|                                 | Week 18 – Week 24: C0-h 80 – 120 ng/ml
(cf. Section 6.5.2 )                                                                                                                                                                 |
| 2) Myfortic ®        | Dose reductions to are possible in case of tolerability problems (cf. Section 6.5.2 )                                                                                                                                          |
| 3) Switch:                      | Introduction of Certican ® and removal of Sandimmun ® Optoral will be performed as described in Section 6.5.1 .                                                                                          |

---

Patients should be seen for all visits on the designated day or as close to it as possible.

Baseline visit 2 assessments and Randomization (Visit 3, Week 7) may be performed in a time window of Week 7 and week 8.

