### **Study design**

Prospective, multi-center, randomized, controlled, parallel group, open-label study in *de novo* senior renal transplant recipients.

For the first 6 weeks post transplantation, all patients will be treated with Simulect® (induction therapy) and immunosuppressive regimen consisting of Myfortic® + Sandimmun® Optoral + corticosteroids (steroids only first 2 weeks).

Control Assessments for renal function will be performed 2 weeks after transplantation.

At Baseline [BL]2 (Visit 3, Week 7) all eligible patients (according to in- and exclusion criteria as specified for BL2) will be randomized to one of the two treatment groups in a 1:2 ratio, stratified by occurrence of rejections between BL1 and BL2:

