#### **Inclusion Criteria**

1. Patients with an stable serum creatinine < 3.0 mg/dl
2. Patients have to be on an immunosuppressive regimen with  $\geq 720$  mg/d Myfortic® and Sandimmun® Optoral
3. Patients with a proteinuria < 500 mg/g creatinine

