Dose increase / adjustment of Certican® and Sandimmun® Optoral should be performed based on the investigator's experience and the given therapeutic blood levels, adverse events, etc. Dose adjustments should be monitored 7 days  $\pm$  2 later (Visit 4).

Sandimmun® Optoral will be administered according to blood trough levels: week 1 – 4 150 – 200 ng/ml (all patients), week 5 – 6: 100 – 150 ng/ml (all patients), week 7 – 18: 100 – 150 ng/ml (only patients in Control group), week 18 – 24: 80 – 120 ng/ml (only patients in Control group).

Myfortic® will be given in both groups according to the "loading dose" regimen: week 1 – 2: 2880 mg/day; week 3 – 6: 2160 mg/day; week 7 – 24: 1440 mg/day.

Corticosteroids will be added to the immunosuppressive regimen according to local standard but with minimum dose of 5 mg/day. Steroids will be withdrawn after week 2 in both groups.

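### Table 4-1 lists removal of Sandimmun Optoral for the Control group in Weeks 3–6, before randomization, against its own footnote and the rest of the protocol

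*Protocol*

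**What the plan says.** Table 4-1 in Section 4 of the protocol sets out treatment by group and period. In the Control block, the Sandimmun Optoral row first gives dosing by blood level, with an asterisk. The next two cells read "removal | Acc. to blood level (see below" (the bar marks the cell boundary), so the removal entry is followed by the cell "Acc. to blood level (see below". In the Certican block, the same row gives dosing by blood level in both prephase cells and no drug after the switch.

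The text describes one prephase for everyone. The synopsis states: "For the first 6 weeks post transplantation, all patients will be treated with Simulect® (induction therapy) and immunosuppressive regimen consisting of Myfortic® + Sandimmun® Optoral". Section 4 says the same for the first six weeks. Section 6.5.1 gives trough targets for this period, among them "week 5 – 6: 100 – 150 ng/ml (all patients". The target table in Section 6.5.2 lists identical ranges for both groups up to Week 6.

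Groups are formed only later: "At BL2 (Week 7, Visit 3), patients whose eligibility is confirmed by additional in- and exclusion criteria will be randomized". One of those criteria, inclusion criterion 2 for Baseline visit 2, begins "Patients have to be on an immunosuppressive regimen with" and names at least 720 mg/d Myfortic together with Sandimmun Optoral. After randomization the Control group continues the regimen it was already on.

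**The concern.** Read literally, the Control cell says that a core immunosuppressant is taken away in the weeks after transplantation and then dosed by blood level again from Week 7. No other passage describes such an interval. The same column also shows corticosteroids being removed and no Simulect, so for the Control group Myfortic would be the only drug listed as given.

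Two things would be at stake if anyone followed the cell. The first is patient safety: Section 1 of the protocol itself reports more acute rejection after early calcineurin-inhibitor withdrawal in regimens based on the related drug MMF. The second is eligibility: a patient still off Sandimmun Optoral at Week 7 would not meet the Baseline 2 criterion and could not be randomized under the protocol.

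**Working it through.** No formula applies and the plan gives no figure to reproduce. The check is to date the cell and then compare it with every other statement about the same weeks.

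**Dating the column.** In Table 4-1 the Myfortic entry in the second prephase column is 2160 mg/day. Section 6.5.1 assigns that dose to a definite period: "week 3 – 6: 2160 mg/day". The corticosteroid removal in the same column fits withdrawal after Week 2. The column therefore covers Weeks 3 to 6, and randomization follows at Week 7.

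**Sandimmun Optoral in Weeks 3–6, by source.**

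| Source in the protocol | Weeks 3–4 | Weeks 5–6 |
|---|---|---|
| Table 4-1, Control row | removal | removal |
| Table 4-1, Certican row | by blood level | by blood level |
| Table 4-1, footnote 1 | 150–200 ng/ml | 100–150 ng/ml |
| Section 6.5.1, all patients | 150–200 ng/ml | 100–150 ng/ml |
| Section 6.5.2, both groups | 150–200 ng/ml | 100–150 ng/ml |
| Synopsis and Section 4, all patients | on the drug | on the drug |

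Only the first row differs.

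**The table against itself.** Footnote 1 runs through Weeks 1–4, 5–18 and 18–24 with no interval left for removal. Footnote 3 does speak of removing Sandimmun Optoral, but ties this to the introduction of Certican and refers to Section 6.5.1, where the switch applies to patients randomized to Certican and starts at Week 7. It cannot explain a Control cell before Week 7. In the other prephase rows (Simulect, Myfortic, corticosteroids, Certican) the two groups match, so this is the only drug for which the table separates groups that do not yet exist.

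**Other rules that meet the cell.** The visit list for Visit 3 (Week 7) draws a cyclosporine trough from patients before they have an arm. Section 6.5.2 says that withdrawal from the study should follow consideration of discontinuation when Sandimmun Optoral is interrupted for more than 14 consecutive days. If the cell meant absence throughout the column, that would be 4 weeks × 7 = 28 days, beyond that limit.

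**Could this be a reading fault in the PDF?** The Control row has its full set of cells and lines up with its neighbours, and the corticosteroid row below has its own separate removal entry. A displaced cell cannot be fully excluded, but it is unlikely.

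**The case against.** The strongest reply is that the cell can hardly be acted on. No patient belongs to the Control group before Week 7, so in Weeks 3–6 no site could identify someone to whom the cell applies. The table also points to its own correction: the row carries the marker for footnote 1, which gives continuous targets and refers to Section 6.5.2. All the other passages agree with each other, so this looks like one mistaken entry, perhaps copied from the corticosteroid row beneath it. All of that stands and limits the weight of the point. It does not make the cell consistent with the rest.

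A reader might infer more than the documents support:

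- **That sites face two real regimens for this drug.** The consistent text and the absence of arms before Week 7 speak against a second intended regimen. That site staff work from this table day to day is not stated anywhere; it is titled as an outline and refers to Sections 6.5.1 and 6.5.2.
- **That the baseline GFR covariate is damaged.** A patient left off the drug would fail inclusion criterion 2, would not normally be randomized, and so would not normally enter the full analysis set or the ANCOVA. A patient taken off and restarted before Week 7 would have been handled so before allocation, so any disturbance could not depend on the assigned arm.
- **That the asterisk is a further error.** It has no matching note in the text available, but the note may have been lost when the PDF was read. Nothing is built on it here.

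**Conclusion.** The contradiction is real and is confined to one cell. Table 4-1 gives an instruction about stopping a core immunosuppressant in Weeks 3–6 that conflicts with its own footnote 1, the matching Certican cell, the synopsis, Sections 4, 6.5.1 and 6.5.2, and Baseline 2 inclusion criterion 2. It is most likely an entry error, and the chance that it was followed is modest. It still needs correcting because it stands in the treatment outline, concerns patient safety and eligibility for randomization, and is cheap to resolve.

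No effect on sample size, power, significance level or the primary analysis is claimed. The conclusion assumes that the cell is printed in the protocol as it was read, and that the Myfortic row dates the column correctly. Which treatment rule holds is for the sponsor to state, not for this review.

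**What to change.** Reconcile the Control group's Sandimmun Optoral cell in Table 4-1 with footnote 1, the matching Certican cell, Sections 4, 6.5.1 and 6.5.2, the synopsis and the Baseline 2 criteria. Make the change by protocol amendment and inform the sites. The sponsor's clinical team decides the content. While the table is open, check against the source file whether the asterisk in that row has a note.

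The cost is one table cell and a short notice to the sites. Showing a single prephase row for all patients would keep the two blocks from drifting apart, but that is optional layout. No statistical section needs to change.

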## 5 Population

The study population will consist of a representative group of approximately 240-260 *de novo* senior kidney transplant patients participating at the Eurotransplant senior program (ESP). These patients will be randomized at Week 7 to either the Control arm or the Certican arm in a 1:2 ratio; 82 patients in the control arm, 164 patients in Certican arm. Enrollment is planned for 24 months, but will be continued until the required sample size will be achieved. The patients will be recruited from about 8 – 12 transplant centers in Germany.

### **Inclusion / Exclusion criteria for Baseline visit (day of transplantation)**

The investigator must ensure that all patients who meet the following inclusion and exclusion criteria are offered enrollment in the study. No additional exclusions can be applied by the investigator, in order that the study population will be representative of all eligible patients.

#### **Inclusion Criteria**

The following inclusion criteria must be present at Baseline visit 1 (BL1, Screening visit prior to transplantation)

1. Males or females, aged > 65 years, receiving the first kidney from a donor aged > 65 years in the Eurotransplant Senior Program
2. Recipients of *de novo* cadaveric kidney transplants

3. Patients who are willing and able to participate in the study and from whom written informed consent has been obtained

#### **Exclusion Criteria**

The following exclusion criteria must not be present at Baseline visit 1 (BL1, Screening visit prior to transplantation)

1. Multi-organ recipients (e.g., kidney and pancreas)
2. Patients receiving a kidney from a non-heart beating donor
3. Patients who are recipients of A-B-0 incompatible transplants
4. Patients with a historical or current peak PRA of > 25% (current = 3 months)
5. Patients with already existing antibodies against the HLA-type of the receiving transplant
6. Patients with any known hypersensitivity to Simulect®, Certican®, mycophenolic acid, cyclosporine A, other drugs similar to Certican® (e.g., macrolides), or other components of the formulations (e.g. lactose)
7. Patients who have received an investigational immunosuppressive drug within four weeks prior to study entry (Baseline visit 1)
8. Patients with thrombocytopenia (platelets < 75,000/mm^3), with an absolute neutrophil count of < 1,500/mm^3 or leucopenia (leucocytes < 2,500/mm^3), or hemoglobin < 6 g/dL
9. Patients with symptoms of significant somatic or mental illness. Inability to cooperate or communicate with the investigator, who are unlikely to comply with the study requirements, or who are unable to give informed consent
10. Patients who are HIV, HCV RNA, or Hepatitis B surface antigen positive
11. Evidence of severe liver disease (incl. abnormal liver enzyme profile, i.e. AST, ALT or total bilirubin > 3 times UNL)
12. Females at randomization who will be not considered post-menopausal according to the following definition:
  - = 12 months of natural (spontaneous) amenorrhea or
  - = 12 month post surgical bilateral oophorectomy or
  - hysterectomized women over or equal to 65 years of age
13. Presence of a clinically significant infection requiring continued therapy, severe diarrhea, active peptic ulcer disease, or uncontrolled diabetes mellitus that in the opinion of the investigator would interfere with the appropriate conduct of the study
14. History of malignancy of any organ system, treated or untreated, within the past 5 years whether or not there is evidence of local recurrence or metastases, with the exception of localized basal cell carcinoma of the skin
15. Evidence of drug or alcohol abuse
16. Patients receiving drugs known to strongly interact with CsA and/or everolimus according to the list provided in [Appendix 3](#) to this protocol should be excluded, if in the opinion of the investigator this drug interaction interferes with the objectives

of the study, namely a clinical meaningful potentiation of renal dysfunction and/or maintenance of adequate immunosuppressive drug levels

### **Inclusion / Exclusion criteria for randomization (Baseline visit 2)**

Of all patients included into the study at BL1 (prior to transplantation), those can continue into the randomized study period, in whom the following condition is observed at BL2, prior to randomization.

